### Sample size calculation

2.10

Sample size calculation was based on the primary outcome (mean pain reduction from baseline to 4 weeks examination), and based on ANOVA statistical test (4 groups). Considering an 80% power, alpha of 5%, and expecting a standard deviation of 2.5 cm, 23 individuals per group (totaling 92 participants) will be required to detect a minimum difference of 2.5 cm in VAS between the groups. In anticipation of a loss of 10% at follow-up, 100 study participants will be included (25 per group). This calculation was based on a study carried out in Brazil,^[16]^ in which the PBMT was effective in reducing the pain of individuals with TMD. The calculation aimed to detect the difference between the active laser groups and SHAM.

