### Assignment of interventions: allocation-sequence generation

2.11

Participants will be randomly assigned to one of the 4 groups with a 1:1 allocation as per a computer-generated randomization schedule using permuted blocks of 4 or 8 participants. The block sizes will not be disclosed to ensure concealment. The sequence generation was provided by one of the researchers ([name]) responsible for the study design but not directly involved with the subject's care.

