### Statistical analysis

2.15

Statistical analysis will be conducted to compare the 4 groups of treatment, concerning the change from baseline of primary and secondary outcomes. Regarding the primary outcome, the groups will be compared using test of comparison of means. If there is adherence to a normal distribution and homogeneity of variances, the groups will be compared by analysis of variance (ANOVA; 2-way repeated measures ANOVA with post hoc Tukey Test). The analysis will be performed by intention to treat, with the imputation of data by carrying forward the last observed outcome in the case of missing data.^[26]^ Groups will be compared as regards other outcome using repeated measures ANOVA or a Chi-squared test. All tests will be conducted considering a 5% alpha.

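### Minor arithmetic error in the sample size section: 100 participants allow for 8% loss, not the stated 10%

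*Protocol article*

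**What the plan says.** All the figures are in section 2.10 (Sample size calculation) of the protocol article. The calculation is "based on ANOVA statistical test (4 groups"), with the settings "Considering an 80% power, alpha of 5"%, "expecting a standard deviation of 2.5 cm" and a target "to detect a minimum difference of 2.5 cm in VAS between the groups". The result is that "23 individuals per group (totaling 92 participants) will be required". The allowance for loss follows: "In anticipation of a loss of 10% at follow-up, 100 study participants will be included (25 per group"). The abstract also gives a total of one hundred.

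Two other sections bear on the point. Section 2.11 has participants "randomly assigned to one of the 4 groups with a 1:1 allocation", so the arms are equal. Section 2.15 (Statistical analysis) plans an intention-to-treat analysis in which missing values are filled by the last observed outcome.

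**The concern.** Section 2.10 makes three linked statements: 92 participants are required, 10% will be lost, and 100 therefore suffice. Any two of them contradict the third. An allowance for loss should leave at least the required number once the loss has occurred, and here it does not.

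What is at stake is the accuracy of the stated justification. A reader would take it that the trial keeps its planned power through a 10% loss, when the margin provided is 8%. The error is confined to the inflation step; the 23 per group before inflation can be reproduced.

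**Working it through.** **Inputs from the protocol article.** Four groups, power 80%, alpha 5%, standard deviation 2.5 cm, difference 2.5 cm, required n of 23 per group (92), anticipated loss 10%, planned n of 25 per group (100): all section 2.10. Equal allocation: section 2.11.

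**Assumption.** Section 2.10 does not give the pattern of the four means. I take 0, 1.25, 1.25 and 2.5 cm: the two extreme groups differ by 2.5 cm and the other two lie midway, which is the least favourable pattern for the overall F test.

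**Step 1: reproduce the plan's 23 per group.** The squared deviations from the grand mean of 1.25 sum to 1.25² + 0 + 0 + 1.25² = 3.125. The noncentrality is n × 3.125/2.5² = 0.5n. With 3 and 4(n − 1) degrees of freedom:

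| n per group | Noncentrality | Overall ANOVA power |
|---|---|---|
| 22 | 11.0 | 78.3% |
| 22.5 | 11.25 | 79.4% |
| 23 | 11.5 | 80.4% |
| 25 | 12.5 | 84.0% |
| 26 | 13.0 | 85.6% |

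The smallest whole n that reaches 80% is 23, which matches the plan. Other patterns need fewer: SHAM against three equal active groups would need 16 per group. The assumed pattern is therefore the one that agrees with the stated figure.

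**Step 2: apply the stated loss to the stated total.**
- 100 × (1 − 0.10) = 90; per group, 25 × 0.90 = 22.5.
- Shortfall against the requirement: 92 − 90 = 2.
- Loss that 100 can absorb: 1 − 92/100 = 8%.

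**Step 3: what a 10% allowance would require.**
- Dividing by the retained fraction: 92/0.90 = 102.2, so 103 in total. Per group, 23/0.90 = 25.6, so 26, or 104 with equal arms. Check: 104 × 0.90 = 93.6, which is at least 92.
- The cruder method of adding 10%: 92 × 1.10 = 101.2, which also exceeds 100.

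**Step 4: cost in power.** From the table, 80.4% at 23 per group falls to 79.4% at 22.5, a drop of 1.0 percentage point.

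**The case against.** **It is only rounding.** Adding 10% to 23 gives 25.3, which is 25 to the nearest whole person. The unrounded requirement under Step 1 is 22.81 per group, and 22.81/0.90 = 25.34, again 25. This probably explains where 25 came from, and against the unrounded total of 91.2 the shortfall is nearer one participant than two. It shows how small the error is but does not remove it: a required size is rounded up, and section 2.10 itself names 92 as the number needed.

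**The planned analysis does not shrink to 90.** This is the stronger objection. Under section 2.15, participants without a four-week value keep their last observed one. Allocation is revealed after the baseline assessment (2.8), and the second assessment follows the first session directly (2.9), so nearly everyone randomised would have a value to carry forward. The nominal number stays at 100, and nominal power at 25 per group is 84.0%. That much stands, and it means 90 should be described as the number with observed four-week data, not as the number analysed.

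It does not make the 10% allowance correct. Section 2.10 inflates from 92 because it treats loss as costing usable participants. Nor does a carried-forward value supply a four-week response: it comes from baseline or from just after the first of eight sessions. As an illustration, suppose 10% in each group carry forward a value with no treatment effect and the standard deviation stays at 2.5 cm. The means shrink to 0, 1.125, 1.125 and 2.25 cm, the noncentrality at 25 per group is 25 × 2 × 1.125²/2.5² = 10.125, and power is about 75%. The actual figure would lie between this and 84.0% to the extent that carried values already contain some of the effect.

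**The stronger reading.** A reader might infer that the trial is underpowered in a way that matters, or that it must enrol 104. The figures do not support that. On observed four-week data the loss is about one point of power, and the lower figure in the illustration reflects the carry-forward method under a pessimistic assumption, not the inflation slip.

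**Conclusion.** The point holds as a minor arithmetic error. On section 2.10's own figures, 100 participants cover a loss of 8%, and a 10% loss would leave 90 with observed four-week data, 2 below the stated 92.

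The 8%, the 90 and the shortfall of 2 need no assumption beyond the stated numbers. The power figures (about 79% against about 80%) rest on the assumed means of 0, 1.25, 1.25 and 2.5 cm and on the protocol's standard deviation of 2.5 cm. The 23 per group is sound under the same assumptions. The design, the outcomes and the enrolment target are unaffected.

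**What to change.** Keep 100 and correct the sentence in section 2.10, for example: *One hundred participants (25 per group) will be included, which allows for a loss of 8% at follow-up.* This is the simpler option and does not conflict with section 2.15.

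If the 10% figure is kept, the sentence should say that about 90 participants would then have observed four-week values and that overall ANOVA power would be about 79% under the stated assumptions. It should add that the intention-to-treat analysis with carry-forward in 2.15 holds the nominal number at 100 but does not restore the lost information. Writing only that 90 remain for analysis would create a new contradiction with 2.15.

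The cost is one sentence and a slightly less favourable stated margin. The total of one hundred in the abstract can stay as it is.

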### Assignment of interventions: allocation-sequence generation

2.11

Participants will be randomly assigned to one of the 4 groups with a 1:1 allocation as per a computer-generated randomization schedule using permuted blocks of 4 or 8 participants. The block sizes will not be disclosed to ensure concealment. The sequence generation was provided by one of the researchers ([name]) responsible for the study design but not directly involved with the subject's care.

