### Assignment of interventions: allocation-concealment mechanism and implementation

2.12

Once the participant is included in the study, the researcher responsible for the conduction of the PBMT will open a sequentially numbered, opaque, sealed envelope that reveals the participant's allocation group. The sealed opaque sequentially numbered envelope was provided by one of the researchers ([name]) responsible for the study design but not directly involved with the subject's care.

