### Trial status

3.1

Participants recruitment began at February 2018 and it is expected to end at October 2021. As shown on Figure 3, 1545 volunteers were screened, 457 participants fitted the study's inclusion criteria, 325 participants were discharged according to exclusion criteria, 132 received the educational measures, and only 40 were included in the study (34 women and 6 men, aged 19–43 years old, mean age 28.4 years). No side effects have been reported so far.

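### Section 2.11 promises that block sizes stay undisclosed to protect concealment, but publishes them (4 or 8) with about 60 of 100 patients still to be randomised

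*Protocol article*

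**What the plan says.** The section on allocation-sequence generation (2.11) states: "Participants will be randomly assigned to one of the 4 groups with a 1:1 allocation", from a computer-generated "randomization schedule using permuted blocks of 4 or 8 participants". The next sentence reads: "The block sizes will not be disclosed to ensure concealment". The list came from a researcher who helped design the study and is not directly involved in care.

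Under the allocation-concealment mechanism (2.12), once a participant is in the study, "the researcher responsible for the conduction of the PBMT will open a sequentially numbered, opaque, sealed envelope". The section on PBMT protocols (2.8) places this at the first treatment session, after the two-week self-care period and the T1 evaluation. The Discussion accepts that the care provider cannot be blinded.

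The Trial status section (3.1) says: "Participants recruitment began at February 2018 and it is expected to end at October 2021". Of those screened, "only 40 were included in the study". The target in 2.10 is 100, or 25 per group. Recruitment is from one clinic (2.3), and no stratification is described.

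**The concern.** Withholding block sizes matters because permuted blocks force balance at known points. Someone who has seen the past allocations and knows the possible sizes can sometimes deduce the next one. Here the document that gives non-disclosure as the protection makes the disclosure, in a journal article open to all trial staff, while recruitment is still running.

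The design makes the information usable. There is one centre, apparently one list, and four arms at equal allocation, so a block of 4 contains each arm exactly once. The therapist accumulates the allocation history by opening the envelopes.

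What is at stake is selection of the next patient. Entry needs a self-reported VAS pain score above 4 after self-care. Those who qualify are then invited, and trial staff arrange the appointments. Foreknowledge of the next arm could influence who is invited or booked into that slot. Blinded outcome assessment does not repair a difference between arms that arises at entry.

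**Working it through.** **Inputs.** Four arms, equal allocation, block sizes 4 or 8 (2.11); target 100 (2.10); 40 included (3.1). The documents do not give the mix of sizes, so I assume 4 and 8 are equally likely, chosen at random for each block.

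**Patients affected.** 100 − 40 = 60, taking included to mean randomised, at the status date of the article.

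**Limiting cases: every block has one known size.**
- Size 4: the best guess is right (1/4)(1/4 + 1/3 + 1/2 + 1) = 0.521 of the time. The last place is certain, so 1/4 = 25% of allocations are certain.
- Size 8: the last place is always certain. The seventh is also certain when the last two places hold the same arm, which has probability 1/7. So (1 + 1/7)/8 = 14.3% are certain. The correct-guess rate by simulation is 46% to 47%.

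**The actual design, sizes mixed and their order unpublished.** After three different arms, the observer cannot tell a block of 4 about to close from a block of 8 under way, so certainty is much rarer than in the limiting cases. I simulated lists of 100 patients. For each patient, the observer's probability for each arm was computed from all past allocations, summing over every division into blocks that fits the history. Chance is 1/4 = 25%.

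| True sizes | What the observer believes | Correct guess | Next arm certain | At least one arm excluded |
|---|---|---|---|---|
| 4/8 | 4 or 8 (as published) | about 48% | about 7% | about 29% to 30% |
| 4/8 | 4, 8, 12 or 16 | about 48% | 0% | 0% |
| 4/8 | nothing; guesses the least-used arm so far | about 48% to 49% | – | – |
| 8/12/16 | 8, 12 or 16 | about 43% | about 2% | about 11% |

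Restricting the first row to patients 41 to 100 gives about 49% correct and 7% to 8% certain.

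**Reading the table.**
- The first three rows have the same guess rate, so publication does not change it. It follows from small blocks with a visible history.
- What publication adds is certainty: from 0% to about 7%, and from 0% to about 29% with an arm excluded.
- Over 60 remaining patients this is about 0.07 × 60 ≈ 4 with a certain next arm and 0.29 × 60 ≈ 17 with at least one arm excluded.
- The last row lets the observer know the new sizes. If they stay unpublished, certainty would be lower still.

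**The case against.** The strongest reply is that the main protections are untouched. The sequence is computer-generated by someone not directly involved in care. The envelopes are sealed, opaque and numbered, and are opened only after inclusion and T1. The outcome examiner is blinded. The sentence could also be meant narrowly, as withholding from site staff which size applies where, and that order is indeed unpublished. The guess rate of about 48% needs no knowledge of block sizes, so setting it against 25% would blame publication for a property of any list with small blocks. Finally, the text does not say that the therapist decides eligibility.

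Most of this stands and limits the point. A reader might infer that the last place in every block is predictable, hence 25% or 12.5% of allocations. That requires knowing the size of the current block, which the article does not reveal. A reader might also infer that the therapist selects patients. The documents do not show this; evaluations are done by a blinded examiner, and masked names prevent any check of overlap with those who schedule. Nor is biased pain reporting the route, since participants are blinded by the sham device.

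Two things do not stand. The narrow reading is not what the sentence says, because it refers to block sizes without limit. And opening an envelope after that patient's own inclusion does not stop the history being used to anticipate the next patient's arm.

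**Conclusion.** The contradiction within 2.11 is real, and it mattered at the status date, with about 60 of 100 patients to come. Publication of the sizes makes the next arm certain for about 7% of patients and allows at least one arm to be excluded for about 29%, for an observer with the full allocation history. These figures assume sizes 4 and 8 are equally likely, one unstratified list, and an observer who makes full use of the history, so they describe what could be deduced rather than what anyone did.

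It would be too strong to say that concealment has failed: there is no evidence that it was broken, and the sealed envelopes still hide the next card. The remaining risk is modest and concerns who is invited or booked next. No bias in the VAS result can be calculated from the documents, and sample size, power and alpha are unaffected. Because the remedy is cheap and recruitment was open, it is still worth making.

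**What to change.** 1. The researcher not involved in care redraws the unused allocations with new, unpublished block sizes that include larger multiples of 4, and reseals the unused envelopes. As an example, 8/12/16 gives about 43% correct guesses and about 2% certain allocations, even to an observer who knows those sizes. If that example were used, different sizes should be chosen in practice so that they are not known.
2. Keep the new sizes out of every document available to trial staff until recruitment closes.
3. Correct 2.11 so that it no longer claims non-disclosure of sizes it has just given, and record the date and envelope number from which the new list applies.

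Rewording the sentence alone would not help, because the published sizes would still apply to the remaining envelopes. A further rule fixing eligibility and T1 before the envelope is opened would mostly repeat the order already set in 2.8 and 2.12.

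**Cost.** A new list and about 60 envelopes. Final group sizes may be slightly less equal: a block cut off when recruitment stops can leave two arms up to 16/4 = 4 apart with a block of 16, against 8/4 = 2 with a block of 8. That is small beside 25 per group.

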### Assignment of interventions: allocation-concealment mechanism and implementation

2.12

Once the participant is included in the study, the researcher responsible for the conduction of the PBMT will open a sequentially numbered, opaque, sealed envelope that reveals the participant's allocation group. The sealed opaque sequentially numbered envelope was provided by one of the researchers ([name]) responsible for the study design but not directly involved with the subject's care.

### Blinding

2.13

All participants will undergo the same clinical conditions, and are therefore blinded to their allocation. Sham procedure will guarantee blinding of participants, as the equipment used to PBMT sessions for G1 has the same design as the active equipment, emits an inert guide light and the same noise as the laser equipment used to treat the other groups. The researcher ([name]) responsible for measuring the study outcomes is also blinded to treatment allocation, characterizing the study as double-blinded. This professional will be responsible for feeding data into the computer in separate datasheets for further analysis without having access to information about the allocation at that moment.

### Participant timeline

2.14

Figure 2 shows participant timeline.

**Figure 2 F2:**
[figure not shown]
Schedule of enrolment, interventions, and assessments (SPIRIT 2013). PPT = pressure pain threshold, RDC/TMD = Research Diagnostic Criteria for Temporomandibular Disorders, TMD = temporomandibular disorder, VAS = visual analog scale.

### Statistical analysis

2.15

Statistical analysis will be conducted to compare the 4 groups of treatment, concerning the change from baseline of primary and secondary outcomes. Regarding the primary outcome, the groups will be compared using test of comparison of means. If there is adherence to a normal distribution and homogeneity of variances, the groups will be compared by analysis of variance (ANOVA; 2-way repeated measures ANOVA with post hoc Tukey Test). The analysis will be performed by intention to treat, with the imputation of data by carrying forward the last observed outcome in the case of missing data.^[26]^ Groups will be compared as regards other outcome using repeated measures ANOVA or a Chi-squared test. All tests will be conducted considering a 5% alpha.

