### Eligibility criteria

2.4

Inclusion criteria: aged between 18 and 50 years; both genders; diagnosis of myalgia and arthralgia, with or without disk displacement; report of TMJ-related pain greater than score 4, measured with visual analog scale (VAS), after 2 weeks of guided self-care; and literate.

Exclusion criteria: patients with muco-supported dental prostheses, orthopedic, or orthodontic appliances; whose state of health contraindicates some of the therapies; presenting teeth in precarious conditions, for example, with indication of endodontic treatment; carriers of rheumatoid arthritis; who are using any analgesic, anti-inflammatory, antidepressant, and/or anxiolytic drugs; carriers of congenital problems with involvement of TMJ and/or cervical region; with recent mandibular fractures; pregnant women; and who are already being treated for TMD in another service.

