### Outcomes and data collection

2.9

Evaluations will be performed by a single trained examiner ([name]) who is blinded to the allocation of the participants within the different treatment groups. Measurements will be performed at the following times: initial (T1), immediately after the 1st PBMT session (T2), at the end of the treatment (T3), and 30 days after the end of therapies (T4).

The primary outcome of the study will be pain reduction (baseline – 4 weeks) according to a visual analog scale of 10 cm. Pain reduction will be expressed in centimeter, as mean group values.

Secondary outcomes will be:

1.Pressure pain threshold in the TMJ, masseter, and anterior temporal muscles, bilaterally, with a digital algometer, registered in kgf (Pain Test Algometer FPX 25; Wagner Instruments).2.Extension of mandibular range of movement, such as mouth opening (taking into consideration the overjet), protrusion (added the overbite), and right and left mandibular movement (noting possible midline deviation) in centimeter, with the aid of a digital caliper.

At each PBMT session, spontaneously reported adverse events and other unintended effects of trial interventions will be registered and managed according to the participant's need.

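### Section 2.15 compares unadjusted change from baseline; using the T1 value already collected as a covariate would be a free improvement, probably modest for the primary VAS

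*Protocol article*

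**What the plan says.** Four sections of the protocol article fix the quantity analysed.

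- Section 2.9: "The primary outcome of the study will be pain reduction (baseline – 4 weeks) according to a visual analog scale of 10 cm". It adds: "Pain reduction will be expressed in centimeter, as mean group values".
- Section 2.10 sizes the trial on the same quantity: "based on the primary outcome (mean pain reduction from baseline to 4 weeks examination), and based on ANOVA statistical test (4 groups").
- Section 2.15: "Statistical analysis will be conducted to compare the 4 groups of treatment, concerning the change from baseline of primary and secondary outcomes". If normality and equal variances hold, "the groups will be compared by analysis of variance (ANOVA; 2-way repeated measures ANOVA with post hoc Tukey Test").
- Section 2.4 restricts entry by pain score: "report of TMJ-related pain greater than score 4, measured with visual analog scale (VAS), after 2 weeks of guided self-care".

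No section names a baseline covariate. Section 2.11 describes permuted blocks of 4 or 8 and mentions no stratification on baseline pain. Section 2.9 schedules measurements at T1, so a baseline exists for every outcome.

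**The concern.** A change score subtracts the whole baseline value, which amounts to assuming that a patient 1 cm higher at T1 would be 1 cm higher at T3 under the same treatment. If the true slope differs from 1, two things follow. The comparison has more variance than it needs, and a chance T1 difference between arms is carried into the treatment contrast. With 25 per arm and no stratification on pain, some chance difference is to be expected.

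The repeated measures ANOVA does not remove this. With T1 and T3 alone, its group-by-time test is the ANOVA on change. With all four times the test differs, but it still does not condition on T1. What is at stake is precision, and the reading of the single randomisation that the trial will have.

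**Working it through.** **Inputs.** From section 2.10: "Considering an 80% power, alpha of 5%, and expecting a standard deviation of 2.5 cm", and "23 individuals per group (totaling 92 participants) will be required to detect a minimum difference of 2.5 cm in VAS between the groups"; 25 per arm enrolled. From sections 2.4 and 2.5: entry above 4 on a 10-cm line. Not in the documents, hence assumed: r = 0.3, 0.5, 0.7; T3 SD s1 = 2.5 cm; T1 SD s0 = 1.2–2.0 cm. The s1 value borrows the only SD that the plan gives. Read literally, that SD belongs to the change, but the percentage gain depends only on r and the ratio s0/s1.

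**1. The plan's own figure.** One-way ANOVA, four groups, two means 2.5 cm apart and the other two midway: f = √(2 × 1.25² / 4) / 2.5 = 0.354. The noncentral F gives 80.4% power at 23 per group and 78.3% at 22. The stated 23 reproduces.

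**2. Plausible T1 SD.** Qualifying scores lie between 4 and 10. A uniform spread has SD 6/√12 = 1.73 cm. The largest possible SD is (10 − 4)/2 = 3.0 cm, with half the patients at each end.

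**3. Formulas.**
- Var(change) = s0² + s1² − 2·r·s0·s1
- Var(ANCOVA) = s1²(1 − r²)
- The difference is (s0 − r·s1)², which is never negative.
- True slope β = r·s1/s0. Given a T1 difference d0 between two arms, the change-score contrast shifts by (1 − β)·d0.
- SE of a chance T1 difference at 25 per arm = s0·√(2/25) = 0.283·s0.

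**4. Primary VAS, s1 = 2.5 cm.** Gain = (s0 − r·s1)² / Var(change). Example, s0 = 2.0 and r = 0.3: (2.0 − 0.75)² / (4 + 6.25 − 3) = 1.5625/7.25 = 22%.

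| s0 (cm) | Gain at r = 0.3 / 0.5 / 0.7 | Slope β | SE of T1 difference (cm) | Shift for 1 SE, \|1 − β\|·SE (cm) |
|---|---|---|---|---|
| 1.2 | 3% / 0% / 9% | 0.63 / 1.04 / 1.46 | 0.34 | 0.13 / 0.01 / 0.16 |
| 1.5 | 9% / 1% / 2% | 0.50 / 0.83 / 1.17 | 0.42 | 0.21 / 0.07 / 0.07 |
| 1.73 | 14% / 5% / 0% | 0.43 / 0.72 / 1.01 | 0.49 | 0.28 / 0.14 / 0.01 |
| 2.0 | 22% / 11% / 2% | 0.38 / 0.63 / 0.88 | 0.57 | 0.35 / 0.21 / 0.07 |

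Eleven of the twelve gains are under 15%. The largest 1-SE shift, 0.35 cm, is 14% of the 2.5 cm target. In four of the twelve cells the slope exceeds 1, so the shift reverses sign.

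**5. Secondary outcomes.** Eligibility sets no cut-off on pressure pain threshold or mandibular movement, so equal T1 and T3 SDs are a reasonable scenario, though not a documented one. Then Var(ANCOVA)/Var(change) = (1 + r)/2, which is 0.65, 0.75 and 0.85: a reduction of 35%, 25% and 15% at r = 0.3, 0.5 and 0.7.

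**The case against.** The strongest reply is that nothing here is an error. Outcome definition, sample size and analysis all use change from baseline, so the plan is consistent. Randomisation makes the change-score contrast unbiased over repeated allocations, and the power was set on change. All of this stands, and it is why the point is an improvement and not a correction.

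Three stronger readings are tempting, and the documents do not support them.

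- **A large power gain for the primary VAS.** With equal T1 and T3 SDs and a change SD of 2.5 cm, ANCOVA power at 23 per arm would be 94.7%, 91.0% and 86.9% at r = 0.3, 0.5 and 0.7. That requires a T1 SD of 2.5/√(2(1 − r)) = 2.11, 2.50 and 3.23 cm. The last exceeds the 3.0 cm maximum under the entry rule, and 2.50 needs scores piled at both ends of the range.
- **An arm that starts higher by chance always looks better.** This needs a slope below 1. Where the cut-off compresses the T1 SD, the slope can exceed 1 and the higher-starting arm then looks worse.
- **Regression to the mean from the entry rule biases the comparison.** It acts on all randomised arms alike in expectation.

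Two further replies stand in part. The inequality in step 3 ignores the cost of estimating the slope: in a simulation with s0 = 1.2, r = 0.5 and 23 per arm, ANCOVA variance was about 1% larger. Also, section 2.5 records spontaneous and palpation pain separately, so the VAS used for entry may not be the VAS analysed, and the compression is then less certain. A covariate might be named in a fuller plan not shown here, but the change-score comparison is what this document states.

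**Conclusion.** The point holds as a free improvement. The planned test is valid, unbiased over randomisations and powered as stated. Its weakness is that it fixes at 1 a slope that could be estimated from data already scheduled for collection. For the primary VAS the likely benefit is modest and could be close to nil; the range in step 4 rests on assumed values of r, T1 SD and T3 SD. The case is stronger for the secondary outcomes, conditional on equal SDs at T1 and T3. Because the slope is unknown and may lie on either side of 1, neither the size nor the direction of the shift from a chance T1 imbalance can be stated in advance. That is itself a reason to estimate the slope.

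**What to change.** Amend section 2.15 to pre-specify ANCOVA of the T3 value with its own T1 value as covariate, for the VAS and for each pressure pain threshold and mandibular movement outcome. Report baseline-adjusted mean differences between groups with 95% confidence intervals, and make the planned pairwise comparisons on the adjusted means. Keep raw mean pain reduction in cm as a descriptive result. The definition in section 2.9 can stay, since with T1 in the model the group contrast is the same, apart from sign, whether T3 or the reduction is the response.

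The cost is a short change of wording and one error degree of freedom per outcome (87 in place of 88 at 23 per arm). No visit, measurement or participant is added. Section 3.1 reports 40 participants included so far, so the change can be dated and recorded before any unblinded analysis.
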